### Follow-up

Table 3 summarises participants’ follow-up during the trial. All participants are monitored for a 6-month period post-randomisation. During the treatment phase, all children are followed once a week in outpatient consultations in each arm. On discharge from treatment, or immediately after inclusion for MAM children aged over 2 years in the standard arm, children are consulted once a month at home until the 6 months post-inclusion is completed. During village visits, a nurse research officer assisted by one or two CHWs monitored the anthropometric and clinical status of these children, referring any child who needed nutritional or medical care to either the primary healthcare facility or to the Mirriah hospital.

**Table 3 Tab3:** Schedule of enrolment, interventions, and assessments, OptiMA Niger

	Admission	Outpatient follow-up	Home visits	6-month post randomisation
Timeline	d0	4–16 weeks^1^	2–5 months^2^	
Frequency	Day	Weekly	Monthly	
**Enrolment**				
Eligibility screening	x			
Individual consent	x			
Randomisation	x			
Socio-demographic data	x			
Economic data	x	x^3^		
Vaccination data	x	x^3^		
**RUTF supplementation**				
Standard	x	x		
OptiMA	x	x		
ComPAS	x	x		
**Assessments**				
Nutritional and medical assessment	x	x	x	x
Hospitalisation if required		x	x	x
Adverse event		x	x	x

^1^Minimum of 4 weeks of RUTF supplementation and a maximum of 16 weeks for the first episode of AM and if relapse

^2^After discharge from the outpatient visit or for children not eligible for supplementation (standard arm aged 24–59 months with a MUAC 115–124 mm and WHZ > − 3 and no oedema)

^3^At the discharge outpatient visit

Failure to reach recovery criteria is defined after 16 weeks in the programme, then children are discharged from OTF as non-responders and consulted once a month at home until they reach the 6-month post-inclusion. For each non-responder discharged with a MUAC < 115 mm, a medical committee meets to decide on the medical follow-up of the child in the trial. Defaulters are defined as a child absent for 3 consecutive visits. CHWs trace children who are absent to motivate caretakers to return to the health facilities. If caretaker refuse to return to the health centre, the child is followed up once a month at home until the 6-month post inclusion period. When caretakers refuse the follow-up at home, the exit status of children is declared “confirmed defaulter” when the vital status is known and “lost to follow-up” when the vital status is unknown.

Children are discharged from outpatient treatment according to the anthropometric exit criteria of their allocation arm. In standard protocol, children need to achieve a MUAC ≥ 125 mm and a WHZ ≥ − 2 without oedema for two consecutive weeks while in OptiMA and ComPAS strategies, children will be discharged if they reach a MUAC ≥ 125 mm without oedema for two consecutive weeks. For each arm, all children will have to participate a minimum of 4 weeks in the programme with good clinical health (absence of fever) to be discharged from the OTF.

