## Abstract

**Background:**

Simplified approaches of acute malnutrition (AM) treatment have been conducted over the past 5 years intending to unify processes and increase coverage among children aged 6 to 59 months without medical complication. The Optimsing treatment for Acute Malnutrition (OptiMA) and the Combined Protocol for Acute Malnutrition Study (ComPAS) are mid-upper arm circumference (MUAC)-based approaches treating children with MUAC < 125 mm or oedema with one sole product—ready-to-use therapeutic food—at a gradually tapered doses. This trial aims to compare the OptiMA and ComPAS strategies to the standard nutritional protocol of Niger assessed by a favourable outcome in the treatment of uncomplicated AM at 6 months post-randomisation and in terms of recovery rate after treatment of uncomplicated SAM (WHZ < − 3 or MUAC < 115mm or oedema) and among the most vulnerable children (MUAC < 115mm or oedema).

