### Study outcomes

The primary outcome will be judged by a binary composite indicator. Children classified as “favourable outcome” fulfil all of the following criteria: alive, not acutely malnourished per the anthropometric definition applied at inclusion (MUAC > 125mm and WHZ > − 3, and no oedema) and not having an additional episode of AM throughout the 6-month observation period. This outcome is measured at 6 months after randomisation. All other children are classified as “unfavourable outcome”.

The main secondary outcome #1 will be determined among children who meet the current WHO definition of SAM at inclusion (MUAC < 115 mm or WHZ < − 3 or oedema +, ++). The main secondary outcome #2 will be determined among children admitted with a MUAC < 115mm or oedema (+, ++). For these two subgroups, recovery is defined in each arm by a 4-week minimum duration of treatment, an axillary temperature < 37.5 °C, and an absence of bipedal oedema and a MUAC ≥ 125 mm for two consecutive weeks. This outcome is measured throughout the 6 months post-randomisation, meaning a child will be considered as recovered if he reaches these criteria during the 6-month follow-up in outpatient or village visits. Additional secondary outcomes are listed in Table 1.

**Table 1 Tab1:** Primary and secondary outcomes in the OptiMA Niger trial

	Measurement variable	Method of aggregation	Time point

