### Randomisation

Randomisation was performed using specially developed software, containing lists prepared in advance by an independent statistician, and inaccessible to trial staff. The randomisation is done in blocks (block size is kept confidential) and stratified at the study site by the severity of AM according to the following criteria: MUAC < 115 mm or oedema, MUAC > 115 mm and WHZ < − 3, and MUAC between 115 and 124 and WHZ > − 3 without oedema. This stratification allows for the recruitment of comparable groups of SAM WHO, MUAC < 115 mm, and non-SAM children and for simultaneous randomisation at the four sites. Once the randomisation was decided by the investigator on the basis of the verification of the eligibility criteria, they interrogated this software, which assigned the code and the corresponding treatment. This software assigns a treatment arm by sequentially drawing from this list each time a randomisation procedure is completed. After the children were assigned to an arm by the software, the trial and clinic staff were informed of the assigned treatment and therefore became unblinded. Once the sample size for the primary objective will be reached, only SAM WHO and then MUAC < 115 mm or oedema children will continue to be enrolled and randomised until the sample size required for the two main secondary objectives will be attained.

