### Intervention

Table 2 summarises the difference in treatment eligibility, recovery definition, and exit criteria between the current national protocol in Niger, OptiMA, and ComPAS strategies. The RUTF ration per week according to standard, OptiMA, and ComPAS strategies are detailed in Additional file 3.

**Table 2 Tab2:** Wasting definition, treatment products, calculation of dosage, and recovery definition in the Niger national, OptiMA, and ComPAS protocols

	National Niger protocol			OptiMA protocol			ComPAS protocol	
	SAM	MAM		Acute malnutrition			Acute malnutrition	
*Wasting definition*	MUAC < 115 mm or WHZ < − 3 or bipedal oedema	MUAC (115–124 mm) or − 3 < WHZ < − 2 and without bipedeal oedema		MUAC < 125 mm or bipedal oedema			MUAC < 125 mm or bipedal oedema	
				MUAC < 115 mm or bipedal oedema	MUAC 115–119 mm	MUAC 120–124 mm	MUAC < 115 mm or bipedal oedema	MUAC 115–124 mm
*Treatment product and quantity*	RUTF 150–200 kcal/kg/day	If aged 6–23 months: super cereal plus 200 g/day (~ 787 kcal/day) or RUSF, one 92 g sachet/day (500 kcal/day)	If aged 24–59 months: no supplementation	RUTF 170–200 (kcal/kg/day)	RUTF 125–190 (kcal/kg/day)	RUTF 50–166 (kcal/kg/day)	RUTF 1000 kcal/day (2 sachets/day)	RUTF 500 kcal/day (1 sachet/day)
*Calculation of dosage*	According to the weight	Fixed amount, regardless of weight or MUAC status	–	According to MUAC status and weight			According to MUAC status	
*Frequency*	Weekly	Weekly	No visit	Weekly	Weekly	Weekly	Weekly	Weekly
*Recovery definition*	• MUAC ≥ 125 mm AND WHZ ≥ − 2 for 2 consecutive weeks • No oedema for 14 days • 4 weeks of participation in the programme • Good clinical health (no fever)			• MUAC ≥ 125 mm for 2 consecutive weeks • No oedema for 2 consecutive weeks • 4 weeks of participation in the programme • Good clinical health (no fever)			• MUAC ≥ 125 mm for 2 consecutive weeks • No oedema for 2 consecutive weeks • 4 weeks of participation in the programme • Good clinical health (no fever)	

*ComPAS* Combined protocol for Acute Malnutrition Study, *MAM* moderate acute malnutrition, *MUAC* mid-upper arm circumference, *OptiMA* Optimising acute MAlnutrition, *RUSF* ready-to-use supplementary food, *RUTF* ready-to-use therapeutic food, *SAM* severe acute malnutrition, *WHZ* weight-for-height *Z*-score

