In the control arm, children included with a MUAC < 115 mm and/or WHZ < − 3 and/or nutritional oedema are treated weekly with RUTF, according to the Niger national protocol dosage table based on the child’s weight. The Niger protocol provides a RUTF daily caloric intake of 150–200 kcal/kg/day during the entire treatment schedule until recovery in children with SAM. Children under 2 years old included with a MUAC between 115 and124 mm and WHZ > − 3 without bipedal oedema are treated weekly by one sachet of RUSF per day (500 kcal/day) during the course of treatment. However, children over 2 years old meeting the same moderate anthropometric criteria are not eligible for supplementation according to the national MAM programme.

The simplified strategies apply to AM children defined as MUAC < 125 mm or bipedal oedema (+, ++) without medical complications on admission and with a good or moderate appetite test.

In contrast to the weight-based RUTF ration in the national SAM programme, the OptiMA RUTF ration is calibrated to the child’s degree of wasting based on the combination of MUAC status and weight. Thus, more nutritional support is given to the most severely malnourished children and then gradually reduced as the child’s MUAC increased. Children with MUAC < 115 mm or oedema receive 175 kcal/kg per day of RUTF. Children with MUAC 115–119 mm, either at admission or during the course of treatment, receive 125 kcal/kg per day of RUTF, and children with MUAC ≥ 120 mm receive 75 kcal/kg per day of RUTF (with a minimum of one sachet/day) until discharge from the programme.

The ComPAS strategy is the most simplified protocol, not requiring a dosage table and proposing to gradually reduce the dosage according to the child’s MUAC status only during the outpatient follow-up as follows: 2 sachets/day of RUTF to children with MUAC < 115 mm or oedema and 1 sachet/day for children in the 115–124 mm MUAC zone.

For both simplified strategies, children with oedema receive the same RUTF ration as children with MUAC < 115 mm until oedema are resolved, at which point their ration is determined by MUAC and weight.

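### The committee review for 16-week non-responders is triggered by MUAC < 115 mm alone and leaves out children whose oedema persists

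*Protocol article*

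**What the plan says.** The rule is in the Follow-up section of the protocol article, in the text below Table 3. A child who has not met the recovery criteria after 16 weeks leaves the outpatient programme as a non-responder and is then seen monthly at home until month 6. One group gets more: "For each non-responder discharged with a MUAC < 115 mm, a medical committee meets to decide on the medical follow-up" of the child. No other part of the article widens that trigger.

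Elsewhere, oedema is placed alongside MUAC < 115 mm:

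- **Abstract, Background:** recovery is to be assessed "among the most vulnerable children (MUAC < 115mm or oedema").
- **Study outcomes:** "The main secondary outcome #2 will be determined among children admitted with a MUAC < 115mm or oedema" of grade + or ++.
- **Randomisation:** the most severe stratum is MUAC < 115 mm or oedema, and once the primary sample size is reached "only SAM WHO and then MUAC < 115 mm or oedema children will continue to be enrolled and randomised".
- **Intervention:** in both simplified arms "children with oedema receive the same RUTF ration as children with MUAC < 115 mm until oedema are resolved".

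Oedema also prevents discharge as recovered. Table 2 lists "No oedema for 14 days" for the national protocol and an equivalent two-week condition for OptiMA and ComPAS. Footnote 1 of Table 3 limits RUTF to 16 weeks per episode.

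**The concern.** The committee exists to look individually at children who have failed treatment and are still severely malnourished. The protocol treats oedema as a marker of that severity at entry, in stratification, in dosing and in an outcome population, then omits it at the one decision point for treatment failures. It gives no reason for the omission.

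The child affected has MUAC of 115 mm or more at week 16 and still has oedema. In a simplified arm this child is on the highest ration until the oedema clears: 175 kcal/kg/day in OptiMA, and in ComPAS "2 sachets/day of RUTF to children with MUAC < 115 mm or oedema". At week 16 that supply ends with the oedema unresolved, and the stated rule calls for no committee review. A non-responder with MUAC < 115 mm, whom the protocol ranks as equally severe, does get the review.

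What is at stake is the care of individual children. No estimate or error rate is involved.

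**Working it through.** The plan gives no figure to reproduce, so the check applies its rules in order to one case.

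**1. Can such a child be in the trial?** Yes. The Eligibility criteria admit children with MUAC < 125 mm and/or oedema + or ++ and/or WHZ < −3. A child with oedema and MUAC of 115 mm or more can be enrolled. So can a child with oedema and a lower MUAC at entry, whose MUAC may pass 115 mm during treatment.

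**2. Is the child a non-responder at week 16?** Yes, in every arm. Table 2 and the discharge rule in Follow-up require absence of oedema for two consecutive weeks. Oedema at week 16 therefore means recovery has not been met, whatever the MUAC.

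**3. Does the committee meet?** The stated condition is MUAC < 115 mm. With MUAC at 115 mm or more it is false, so no meeting is called for.

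**4. What happens to the ration?** Table 3, footnote 1, ends RUTF at 16 weeks. The footnote allows another course for a relapse, but Table 1 times relapse after recovery from the first episode. A child who never recovered does not clearly qualify.

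**5. How long does this last?** Taking 6 months as about 26 weeks, follow-up remaining for a first-episode non-responder is 26 − 16 = about 10 weeks. One month is 26 / 6 ≈ 4.3 weeks, and 10 / 4.3 ≈ 2.3, so about two monthly home visits are left.

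**6. Does another rule supply the review?**

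| Provision | Section | Covers this child? |
|---|---|---|
| Nurse refers children needing care at home visits | Follow-up | Yes, but it is referral at a monthly visit, not committee review |
| Referral for higher-level treatment; national hospitalisation criteria | Intervention | Yes, if the criteria are met; they are not reproduced in the article |
| Assessment, hospitalisation and adverse-event recording to month 6 | Table 3 | Yes, as monitoring |
| Removal if not SAM at inclusion and deteriorating to SAM during supplementation | Safety | Not if oedema was present at inclusion, and never in the control arm |
| Removal after two episodes of > 5% weight loss plus a hospitalisation | Safety | Intervention arms only, and not triggered by oedema |

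Several provisions give the child access to care. None gives the committee review.

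**The case against.** The strongest reply is that oedema was meant all along. The article often shortens the group to MUAC < 115 mm. The Randomisation section defines the stratum with oedema and then speaks of "the recruitment of comparable groups of SAM WHO, MUAC < 115 mm, and non-SAM children". The Abstract's sample-size sentence, the Introduction and the Discussion use the same shorthand for a population that Objectives and Study outcomes define with oedema. The Follow-up sentence may be one more case. This is plausible and cannot be excluded. If so, the edit only makes explicit what staff already do. But this sentence is an operating instruction for staff at four sites, and its threshold should not have to be inferred.

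A second reply is that an article condenses a longer protocol. That would excuse silence about the committee's membership, timing or remit. It does not excuse a threshold that the article does state and that differs from its own severity grouping.

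A third is that care is covered by weekly assessment during treatment, nurse referral afterwards and national hospitalisation criteria, which may lead to referral of persistent oedema well before week 16. This stands as a limit on the consequence. However, the same provisions apply to non-responders with MUAC < 115 mm, for whom the sponsor still wanted a committee.

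A fourth is that a sponsor may set a committee trigger differently from a stratum or a ration, and that the group may be empty, since oedema +++ is excluded at entry. Both points are fair. They keep the matter minor but do not explain the omission.

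**Conclusion.** The point holds. As written, a week-16 non-responder with oedema and MUAC of 115 mm or more goes to monthly home visits without the committee review given to non-responders with MUAC < 115 mm.

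The number of such children is unknown: the article gives no figure for oedema at entry or at week 16. It is probably small and may be zero. The gap is one missing review, not loss of all care. The rule applies equally in all three arms, and alpha, power and the planned analysis are unaffected. Severity is minor.

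The conclusion assumes that the sentence is followed literally and that no fuller document extends the trigger. Confidence is medium, because the sentence may be shorthand.

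**What to change.** In the Follow-up section, extend the trigger so that the committee meets for each non-responder discharged with MUAC < 115 mm or oedema, worded identically for the three arms. The decision on further care stays with the committee.

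The cost is two words and probably a few more case reviews by a committee that already exists. Oedema is already part of the trial's anthropometry procedure and of every arm's exit criteria, so nothing new has to be measured and the simplified arms keep follow-up by MUAC and oedema only.

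Adding WHZ < −3 as well is not part of this recommendation. It would bring WHZ-based review into arms managed without it. It would also fall more heavily on control children, because simplified-arm children with MUAC of 125 mm or more and no oedema can leave as recovered whatever their WHZ. WHZ is also a component of the primary outcome in an open-label trial.

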**Main secondary**			
Recovery	Composite: absence of bipedal oedema and a MUAC > 125 mm for two consecutive weeks, a 4-week minimum duration of RUTF treatment, and a good clinical health (without fever)	Proportion	Throughout the 6-month follow-up period
**Secondary**^a^			
Cost-effectiveness	Incremental cost-effectiveness ratio (ICER)	Ratio	Throughout the 6-month follow-up period
Consumption of RUTF per children with a favourable outcome	Sachets of RUTF consumed	Mean	6-month post-inclusion
Consumption of RUTF per recovered children	Sachets of RUTF consumed	Mean	End of RUTF treatment initiated at inclusion
Average daily weight gain in SAM children recovered	g/kg/day	Daily	End of RUTF treatment initiated at inclusion
Average daily MUAC gain in SAM children recovered	mm/day	Daily	End of RUTF treatment initiated at inclusion
Hospitalisation	Children with at least one episode of hospitalisation	Proportion	Throughout the 6-month follow-up period
Relapse to a new episode	Children with MUAC < 125 or WHZ < − 3 *Z*-score or oedema after RUTF treatment	Proportion	After recovering from the first episode of acute malnutrition
Non-response	Children who did not reach the recovery criteria	Proportion	16 weeks after inclusion
WaST	Children associated with severe and moderate stunting with acute malnutrition	Proportion	Throughout the 6-month follow-up period

^a^All the secondary outcomes will be analysed for the overall population (MUAC < 125 mm or WHZ < − 3 or oedema) and for the secondary populations (SAM WHO and MUAC < 115 mm or oedema)

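### The Table 1 relapse definition counts a WHZ < −3 that never resolved as a new episode, mainly in OptiMA and ComPAS, because only the control arm requires WHZ recovery before discharge

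*Protocol article*

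**What the plan says.** **Relapse.** In Table 1 (Study outcomes), the row on relapse to a new episode has the measurement variable "Children with MUAC < 125 or WHZ < − 3", or oedema, after RUTF treatment. Its time point is "After recovering from the first episode of acute malnutrition". The definition is the same in all arms. The footnote adds "All the secondary outcomes will be analysed for the overall population" as well as for the two severe subgroups. The Objectives section lists relapse among the outcomes compared between the three arms.

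**Discharge.** For the national protocol, Table 2 (Intervention) requires "MUAC ≥ 125 mm AND WHZ ≥ − 2 for 2 consecutive weeks". For the other two arms, the Follow-up section says "in OptiMA and ComPAS strategies, children will be discharged if they reach a MUAC ≥ 125 mm without oedema for two consecutive weeks". Children who have not met the exit criteria after 16 weeks are "discharged from OTF as non-responders" and then seen monthly at home. Defaulters who will not return to the health centre are also followed monthly at home.

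**Trial recovery.** Under Study outcomes, "recovery is defined in each arm by a 4-week minimum duration of treatment", together with no fever, no oedema and MUAC ≥ 125 mm for two consecutive weeks. It has no WHZ term.

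**Who is at risk.** The Randomisation section gives children with WHZ < −3 and MUAC above 115 mm their own stratum, so they enter all three arms. WHZ < −3 can also occur in the MUAC < 115 mm stratum.

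**Gate.** Under Statistical analysis, the other secondary comparisons are run only if non-inferiority is shown for favourable outcome and recovery.

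**The concern.** A relapse outcome should record deterioration after recovery. As published, the measurement variable does not require WHZ to have been at or above −3 before a later value below −3 counts. In control, discharge as recovered means WHZ ≥ −2, so a later WHZ < −3 is a fall of more than one Z-score. In OptiMA and ComPAS, the same finding can be a deficit present from enrolment. The same words measure deterioration in one arm and partly persistence in the other two.

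At stake is how a secondary result is read. Relapse is examined only once a simplified strategy has passed non-inferiority. An artefactual excess would then look like the price of an otherwise acceptable strategy. It would also blur two different messages for programmes: that a MUAC-only exit leaves some WHZ deficits untreated, or that recovery under a tapered ration does not last.

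**Working it through.** **1. The rules applied to one child.** Take a child with MUAC 126 mm and WHZ −3.2 for two weeks, no oedema, no fever and at least four weeks of treatment, with the same values at the next monthly home visit.

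| | OptiMA or ComPAS | Control |
|---|---|---|
| Meets trial recovery (no WHZ term) | yes | yes |
| Discharged as recovered | yes | no, WHZ must reach −2 |
| Treatment stops | now | at WHZ ≥ −2, at 16 weeks as non-responder, or on default |
| Home visit at WHZ −3.2 scored as relapse | yes, with no change in status | only after non-responder or defaulter exit |

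The direction therefore follows from the text. The state is foreseeable: the Eligibility criteria section itself notes that WHZ < −3 with MUAC ≥ 125 mm lies outside the definition of wasting in both simplified strategies.

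**2. Routes in control.** A control child is scored the same way after meeting MUAC-only recovery with WHZ still < −3 and then leaving treatment (a) at 16 weeks as a non-responder, or (b) as a defaulter followed at home. Children with WHZ < −3 and MUAC ≥ 125 mm, who are placed in control without randomisation, already meet the MUAC threshold at entry. If they are analysed with control, they can use either route. The asymmetry remains but is not absolute.

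**3. Illustration of size.** The article does not give the share of recovered children discharged with WHZ < −3, so that share, *u*, is assumed.

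Inputs from the Sample size section: 295 per arm for the WHO-defined SAM population, 82% recovery, 5% inflation, pilot relapse 30%. From Statistical analysis: two-sided 5% tests.

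The plan's own figure first: 2 × 0.82 × 0.18 × (2.2414 + 0.8416)² / 0.10² = 280.6, and 280.6 × 1.05 = 294.6, which reproduces 295.

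Evaluable per arm: 295 / 1.05 ≈ 281. Recovered per arm: 281 × 0.82 ≈ 230.

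With true relapse *r* equal in both arms and carry-over independent of other relapse, scored relapse is *r* in control and *r* + *u*(1 − *r*) in a simplified arm. The chance of a significant excess in the simplified arm comes from exact binomial enumeration of the pooled two-proportion z test at two-sided 5%, with 230 per arm and *r* = 30%:

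| Assumed *u* | Children (of 230) | Scored relapse, simplified arm | Chance of false excess |
|---|---|---|---|
| 0% | 0 | 30.0% | 2.5% |
| 1% | about 2 | 30.7% | 3.6% |
| 2% | about 5 | 31.4% | 5% |
| 5% | about 12 | 33.5% | 13% |
| 10% | 23 | 37.0% | 36% |

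**4. Sensitivity to independence.** Suppose 60% of the carried-over children would have relapsed on MUAC or oedema anyway (also an assumption), with overall true relapse still 30%. Scored relapse becomes 0.30 + 0.4*u*: 32% at *u* = 5% and 34% at *u* = 10%. The chance of a false excess falls to 6.8% and 15%.

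**The case against.** **The row title already says new episode.** An unresolved deficit is not new in ordinary reading, and turning visits into episodes is often left to the analysis plan, which is not shown. That plan may settle the matter. But the published measurement variable and time point, applied as they stand, count the unchanged child. The row's title and its content disagree, and that is a fault in the text itself.

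**One anthropometric standard for all arms may be deliberate.** The primary outcome also requires WHZ above −3 in every arm, and a child off treatment at WHZ < −3 is malnourished by the trial's common definition. This stands: such children must stay visible. It supports reporting them, but not calling them relapses after recovery.

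**The size may be small.** This also stands. At a 1% share the effect is slight, and dependence between persistent low WHZ and later low MUAC shrinks it. The overall population, where WHZ < −3 is less concentrated, would dilute it. The probabilities treat the test as always run, although it is gated; a large share still below −3 at month 6 would also fail the primary outcome and make the gate less likely to open.

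**A stronger reading to resist.** A reader might infer that the primary outcome is affected too, since it requires "not having an additional episode of AM throughout the 6-month observation period" and the Discussion speaks of relapse within the main outcome. The documents do not support this. A persisting episode is not an additional one, and nothing in Study outcomes ties that phrase to the Table 1 relapse row; the only link is a general sentence in the Discussion.

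**Conclusion.** The point holds for the secondary relapse outcome. As defined in Table 1, relapse includes WHZ deficits that never resolved. The arm-specific discharge rules put these mainly in OptiMA and ComPAS, so the comparison is biased against them. A reader might go further and say that control children cannot be scored this way; they can, through non-responder or defaulter exit.

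The direction rests on the text alone. The size cannot be determined: it depends on a share the article does not report, and the 2.5% to 36% range rests on assumed shares, 30% true relapse in both arms, independence and the test being run. Severity is minor to moderate, since one gated secondary outcome is affected and neither the primary outcome nor the sample size is shown to be.

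**What to change.** For the relapse outcome, in every arm:

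- After discharge from treatment, count WHZ < −3 as relapse only if WHZ was ≥ −3 at discharge or at a later visit.
- Keep MUAC < 125 mm and oedema after discharge as they are.
- Report children who leave treatment with WHZ < −3 separately by arm, as first episode unresolved on WHZ.
- Add a sensitivity analysis of relapse that counts these children as events.

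Leave the primary outcome unchanged.

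The cost is one sentence in the outcome definition and one derivation rule. Table 3 already schedules nutritional assessment at outpatient, home and 6-month visits, so no new visit is needed. The downside is that persistent WHZ deficits leave the relapse count. The separate report and the sensitivity analysis cover this, and a child still below −3 at month 6 fails the primary outcome in any case.
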